### **3.4 Randomization and blinding**

#### **3.4.1 Randomization method**

The study adopts the method of stratified block randomization, and subjects will be randomly assigned by 2:2:1:1. The subjects randomization table is generated by an independent randomization professional using SAS version 9.4 or above and imported into the Interactive Response Technology (IRT) system, accessible only to authorized personnel. Non-blind personnel at authorized research centers can obtain grouping information of subjects through the IRT system and use the investigational vaccines for the corresponding group based on it. Other investigators and the sponsor's research management team will be blinded throughout the trial. The laboratory staff will be blinded throughout the trial.

#### **3.4.2 Maintenance of blinding**

Those who administer, prepare and administer vaccines are unblinded staff and must sign a blinding maintenance agreement to ensure that any documents of the unblinding information are only accessible for the authorized non-blinded staff. The labels on vaccine syringe will be covered with a study number label after the preparation of the vaccine and put it ready to use. The unblinding staffs do not allow to participate in other process of the trial.

#### **3.4.3 Unblinding**

The investigator must not disrupt the blind study of the vaccine unless the treatment allocation information is medically necessary for the subjects in emergency. In the case of a medical emergency, the principal investigator should determine need for an urgent unblinding.

Blinding will be uncovered when completing the initial analysis of safety and immunogenicity 28 days after the second dose, but the subjects and safety observers will remain blinded.

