#### **5.5.6 Reporting procedures for SAE**

Any SAE, whether related to injection vaccine or not, must be reported to the principal investigator via fax or E-mail within 24 hours of being informed of the SAE Report Form: This includes descriptions of AE, timing and type of onset, duration, intensity, causality with vaccination, outcomes, management (symptomatic treatment), and other relevant clinical and laboratory data.

Upon receiving the report of a SAE, the principal investigator, together with the safety observer, decided whether the subjects should continue to participate in the study or terminate the study early, taking into account the duration, extent, intensity, outcome and willingness of the subjects. The principal investigator should determine whether the SAE is suspected and not SUSAR. If so, the principal investigator should report to the vaccine manufacturer, the Drug Evaluation Center of the General Administration and the National Health Commission in time.

For suspicious and SUSAR that are fatal or life-threatening, the principal investigator should report to the Drug Evaluation Center of the General Administration as soon as possible after first being informed, but within 7 natural days, and within the following 8 days to improve the follow-up information.

Note: The first day principal investigator be aware of the event is Day 0.

For suspicious and SUSAR of non-fatal or life-threatening, or other potentially SAE, the principal investigator should report to the Drug Evaluation Center of the General Administration as soon as possible after first received the information, but within 15 natural days. SAE should be truthfully recorded, evaluated and discussed in the boost report after completion or termination of the trial.

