### 6.2.3 Initial analysis

An initial analysis of safety and immunogenicity will be performed after completing all the data collection within 28 days after the boost vaccination.

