## 3.2 Randomization and Blinding

### 3.2.1 Randomization

The method of stratified block randomization is adopted in this study, and subjects will be randomly assigned by 2:2:1:1. The subjects randomization table is generated by an independent randomization professional using SAS version 9.4 or above and imported into the Interactive Response Technology (IRT) system, accessible only to authorized personnel. Subjects, investigators and the sponsor's research management team will be blinded throughout the trial. Non-blind personnel at authorized research centers can obtain grouping information of subjects through the IRT system and use the experimental vaccine for the corresponding group based on it.

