### 3.2.3 Unblinding

We masked investigators, laboratory staff, and outcome assessors to the allocation of treatment groups, but not to the three-dose or two-dose regimen. In the event of a medical emergency, the principal investigator should be contacted as far as possible before disrupting the study vaccine/placebo blinding to discuss the need for an urgent unblinding.

Blinding will be uncovered when completing the initial analysis of safety and immunogenicity 28 days after the second dose, but the subjects and safety observers will remain blinded.

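### The unblinding rule at the initial analysis contradicts the blinding promised to investigators and sponsor for the whole trial, which exposes related-SAE, SUSAR and late per-protocol decisions

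*Combined protocol and SAP*

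**What the plan says.** Four statements govern who is blind, and until when.

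- **Lifting the blind.** Protocol 3.4.3 and SAP 3.2.3 share the sentence "Blinding will be uncovered when completing the initial analysis of safety and immunogenicity 28 days after the second dose", which continues "but the subjects and safety observers will remain blinded". No other role is excepted.
- **Blind to the end, protocol.** Protocol 3.4.1: "Other investigators and the sponsor's research management team will be blinded throughout the trial". It adds "The laboratory staff will be blinded throughout the trial", and the synopsis repeats the laboratory promise.
- **Blind to the end, SAP.** SAP 3.2.1: "Subjects, investigators and the sponsor's research management team will be blinded throughout the trial".
- **Timing of the initial analysis.** Protocol 6.2.3, with the same text in SAP 6.10: "An initial analysis of safety and immunogenicity will be performed after completing all the data collection within 28 days after the boost vaccination".

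Some work is still to be done after that analysis. SAEs are collected from Day 28 to Month 6 (protocol 5.5.1). Causality is part of the SAE report, and on expedited reporting protocol 5.5.6 says "The principal investigator should determine whether the SAE is suspected and not SUSAR". SAP 6.6 tests related and unrelated SAEs between groups. SAP 5.1 has the principal investigator and the statistician settle the analysis sets before database lock, without saying whether a lock precedes the initial analysis.

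**The concern.** A rule that lifts the blind for everyone except two named roles cannot stand beside a promise that investigators and the sponsor's team remain blind for the whole trial. Site staff could follow either text and be in breach of the other. The laboratory falls in the gap: it is promised blinding throughout but is not among the exceptions when the blind is lifted.

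The trigger wording adds to the confusion. Subjects in Groups A and B, who carry both hypotheses, had their second dose before they entered the trial.

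At stake are judgements made late in follow-up by people who may by then know the arm and the Day 28 results: whether an SAE is related, whether it is a SUSAR, and whether a participant belongs in the per-protocol set.

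**Working it through.** The plan gives no figure for this point, so the check is mainly a reading of the texts side by side, followed by a bound on the exposed follow-up.

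**1. Who is blind after the initial analysis**

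| Role | Protocol 3.4.1 / SAP 3.2.1 | Protocol 3.4.3 / SAP 3.2.3 exception |
|---|---|---|
| Subjects | blind throughout (SAP 3.2.1) | stay blind |
| Safety observers | not named separately | stay blind |
| Investigators | blind throughout (the protocol excludes the unblinded vaccine staff) | not excepted |
| Sponsor's management team | blind throughout | not excepted |
| Laboratory staff | blind throughout (protocol 3.4.1 and synopsis) | not excepted |

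Investigators and the sponsor's team are in direct conflict. The laboratory is a conflict by omission.

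**2. The trigger.** SAP 3.1 makes the trial dose the third in Groups A and B and the second in Groups C and D. Counting from the second dose therefore fits C and D only. Unblinding is tied to completing the initial analysis, and protocol 6.2.3 and SAP 6.10 place that analysis after the post-boost Day 28 data. The intended date can be recovered, so this is a wording error.

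**3. What is collected before unblinding.** The primary endpoints are the Day 14 neutralising GMT and adverse reactions within 28 days (protocol 3.1.1, SAP 4.1). Both are collected before the blind is lifted. The secondary SAE endpoint is an incidence, and protocol 5.5.5 defines an SAE whether or not it is related, so a causality call does not change it.

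**4. What is left exposed**
- The related/unrelated SAE comparison in SAP 6.6, for events judged after unblinding.
- SUSAR decisions by the principal investigator, who is not among the exceptions (protocol 5.5.6).
- Per-protocol exclusions decided after unblinding. The per-protocol set asks for all blood samplings (protocol 6.2.1, SAP 5.1), and Month 6 is one of them (protocol 4.5.2), so as written membership cannot be final before Month 6.

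**5. Bound on exposed SAE follow-up.** Take Month 6 as Day 180, the day used in SAP 6.4.
- Exposed share at most = (180 − 28)/180 = 152/180 = 84.4%.
- Visit windows are +4 days at V3 and ±15 days at V4. Lowest: (165 − 32)/165 = 133/165 = 80.6%. Highest: (195 − 28)/195 = 167/195 = 85.6%.
- Let L be the days from a subject's Day 28 to the actual unblinding. The exposed share is max(0, 152 − L)/180. The blind is lifted only once all Day 28 data are in and analysed. The documents give neither the enrolment period nor the analysis time, so L is unknown. The share runs from 84% at L = 0 down to zero at L of 152 or more.

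**The case against.** The strongest reply is that the damage is small. This is largely right.

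- **A trigger before the trial.** A reader might infer that the rule unblinds Groups A and B before enrolment. The documents do not support that: an analysis of post-boost data cannot be completed before the boost is given.
- **Month 6 titres read by unblinded staff.** A reader might infer this from the laboratory's absence from the exceptions. Protocol 3.4.1 and the synopsis promise laboratory blinding without exception, SAP 3.2.2 lists the testers as blind, and protocol 10.2.2 says samples carry only ID, random and specimen numbers. The omission calls for a clarifying word; it does not show exposure.
- **Every late SAE call compromised.** Protocol 5.5.4 does not name who assigns the causality code. Safety observers stay blind, and under protocol 5.5.6 they act with the principal investigator on continued participation. The exposure is therefore partial, and it is inferred from the principal investigator's SUSAR role and from investigators completing the SAE form.
- **Every per-protocol exclusion compromised.** The documents do not say whether sets are settled before the initial analysis, and the primary set is the FAS (modified ITT in the SAP). Nor is there any infection adjudication to bias: intercurrent infection appears only as a per-protocol exclusion.

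What remains is the contradiction itself. One could read the unblinding as meant for the analysis team alone, but excepting only subjects and safety observers implies that the remaining roles are not excepted.

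**Conclusion.** The point holds as an internal contradiction with limited consequences. Protocol 3.4.3 and SAP 3.2.3 cannot be followed together with protocol 3.4.1 and SAP 3.2.1 for investigators and the sponsor's team. The laboratory's position needs stating, and the timing wording is wrong for the 200 participants in Groups A and B.

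The primary endpoint data and SAE incidence are not affected. The exposure is confined to relatedness and SUSAR judgements made after unblinding and to late per-protocol exclusions. For SAEs it reaches at most 84% of a subject's follow-up (81% to 86% across visit windows), assuming Month 6 is Day 180 and no delay between Day 28 and unblinding. The true share will be smaller by an amount the documents do not let one calculate, and the size of any bias cannot be derived from them.

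The amendment should be made, because it is cheap and protects a between-group safety comparison that the SAP itself plans.

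**What to change.** In protocol 3.4.3 and SAP 3.2.3:

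1. Replace the words second dose with boost vaccination, to agree with protocol 6.2.3 and SAP 6.10.
2. State that only the statisticians running the initial analysis see individual allocation, and that group-level results may be released.
3. Give one list of the roles that stay blind until the Month 6 database lock: subjects; safety observers; site investigators, including those who judge SAE causality and per-protocol membership; the sponsor's research management team; and laboratory staff. The unblinded vaccine staff remain as already defined.
4. Align protocol 3.4.1 and SAP 3.2.1 with that list.

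Emergency unblinding is unchanged. Freezing per-protocol membership by visit is not needed for this repair, and it would require a new definition because the current set asks for every blood sample.

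The cost is a wording amendment to both documents. The downside is that individual allocations stay restricted for up to about five more months (152 days); group-level results can still be reported in that time.

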### **3.5 Investigational vaccine**

#### **3.5.1 Recombinant COVID-19 vaccine (Ad5 Vector)**

Recombinant COVID-19 vaccine (Ad5 Vector) is a kind of human adenovirus 5

with replication defect which expresses SARS-COV-2 protein and inoculates HEK293SF-3F6 cells. After amplification and purification, the liquid preparation made by adding appropriate excipients is used to prevent the disease caused by SARS-COV-2 infection.

Active ingredient: Recombinant replicated-defective human adenovirus 5 expressing novel coronavirus protein ( $5 \times 10^{10}$  VP) .

Auxiliary material: mannitol, sucrose, sodium chloride, magnesium chloride, polysorbate 80, hydroxyethyl piperazine ethanesulfonic acid, glycerol

Packing: vial

Specifications: 0.5ml/piece ( $5 \times 10^{10}$ VP)

EXP: tentatively 12 months

Storage: Storage and transportation at 2-8°C.

Inoculated Pathway: Intramuscular injection (IM) into the lower margin of the deltoid muscle of the lateral upper arm.

Immunization procedure: single dose.

### **3.5.2 Inactivated SARS-CoV-2 vaccine (Vero cells)**

Manufacturer: Beijing Sinovac Research & Development Co., Ltd.

Specification: 0.5ml/ bottle, for commercial packaging, storage according to the instructions.

EXP: tentatively 12 months

Storage: Storage and transportation at 2-8°C.

Inoculated Pathway: Intramuscular injection (IM) into the lower margin of the deltoid muscle of the lateral upper arm.

Immunization procedure: single dose.

### **3.6 Criteria for pausing or early termination**

The principal investigator will organize an expert panel meeting to decide whether to terminate the clinical trial early, if one of the following situations occurs:

- 1) Occurrence of one or more  $\geq$  grade 4 adverse reaction or serious adverse event that may be associated with vaccination;
- 2) Occurrence of grade 3 adverse events associated with vaccination in 10% of

participants or more.

The study will be terminated in advance if one of the following situations occurs:

- 1) Level 4 adverse reactions or serious adverse events that may be related to vaccination occurred during the study period, an expert group organized by the principal investigator will decide whether to terminate the experiment after discussion;
- 2) Occurrence of grade 3 adverse events associated with vaccination in 15% of participants or more (including injection-site reaction, systemic reaction, and vital signs and abnormal laboratory data;
- 3) The principal investigator calls for a complete termination of the trial and explain the reasons;
- 4) Ethics committee call for a complete termination of the trial and explain the reasons;
- 5) Administrative authority call for a complete termination of the trial and explain the reasons.

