|--------------------------------------------------|-----------------------------------------------------------------------------------------------------------------------------------------------------------------------------------------------------------------------------------------------------------------------------------------------------------------------------------------------------------------------------------------------------------------------------------------------------------------------------------------------------------------------------------------------------------------------------|
|                                                  | 
Exploratory endpoints:
 
 
● Isotypes of binding antibodies IgG against SARS-CoV-2 S protein at Day 14, Day 28 and Month 6 after the boost vaccination;
 
● Cross neutralizing of the antibodies to variants of SARS-CoV-2 at Day 28 after the boost vaccination;
 
● The differentiation of immune cell and antibody spectrum of B cells, T cells and other major immune cell in each group at Day14, Day 28 and Month 6 after the boost vaccination.
 
                                                   |
| Scheduled site visits                     | 
Visit Plan:
 
V1: On day 0, informed consent and sign informed consent form (ICF), physical examination, consultation screening, blood collection before immunization, immunization and observation should be completed;
 
V2: On Day14 after the boost vaccination, safety follow-up and blood collection should be completed;
 
V3: On Day 28 after the boost vaccination, safety follow-up and blood collection should be completed;
 
V4: On Month 6 after the boost vaccination, safety follow-up and blood collection should be completed;
 |
| Criteria for pausing or early termination | 
Criteria for pausing:
 
 
● Occurrence of one or more <math>\geq</math>grade 4 adverse reaction or serious adverse event that may be associated with vaccination;
 
● Occurrence of grade 3 adverse events associated with vaccination in 10% of participants or more.
 
 
Investigators could terminate the study when any criteria for early termination is meet:
                                                                                                                            |

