|                                         | 
 
● One or more <math>\geq</math> grade 4 adverse reaction or serious adverse event occur that may probably associated with vaccination;
 
● Occurrence of grade 3 adverse events associated with vaccination in 15% of participants or more (including injection-site reaction, systemic reaction, and vital signs and abnormal laboratory data;
 
● The principal investigator call for a complete termination of the trial and explain the reasons;
 
● Ethics committee call for a complete termination of the trial and explain the reasons;
 
● Administrative authority call for a complete termination of the trial and explain the reasons.
 
                                                                                                                                                                                                                                                                                                |
| Inclusion and exclusion criteria | 
Inclusion Criteria:
 
 
1. Health subjects aged 18-59 years, who have been completed two-dose regimen of inactive SARS-CoV-2 vaccine in the past 3-6 months, or received one dose of inactive SARS-CoV-2 vaccine in the past 1-3 months.
 
2. The subject can provide with informed consent and sign informed consent form (ICF).
 
3. The subjects are able to and willing to comply with the requirements of the clinical trial program and could complete the 6-month follow-up of the study.
 
4. Axillary temperature <math>\leq 37.0^{\circ}\text{C}</math>.
 
5. Individuals who are in good health condition at the time of entry into the trial as determined by medical history, physical examination and clinical judgment of the investigator and meet the requirements of immunization.
 
 
Exclusion Criteria:
 
 
1. have the medical history or family history of convulsion,
 
 |

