## **5.5 Safety follow up and evaluation**

### **5.5.1 Safety observation**

After vaccination, the participants will stay at the clinic for 30-minute safety observation. The trained researchers should systematically observe each subject,

record the local and systemic reactions within 30 minutes, and record the severity.

The participants are followed for the next a few days, and asked to record the safety observation by themselves on the diary card till 14 days after the vaccination. From the day 15 to the day 28 after vaccination, the adverse events are recorded passively. From day 28 to month 6 after vaccination, the subjects are asked to report only serious adverse events during this period.

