### 5.5.2 Safety observation contents and indicators

Adverse events from the clinical trial are graded according to the guiding principles for the classification of adverse events in clinical trials of preventive vaccines (NMPA [2019] No. 102), as follows: (table 3-4)

**Table 3** Grading of (local) AEs at injection site

| Symptoms                                                 | Grade 1                                                                                               | Grade 2                                                                | Grade 3                                                                                                                                                              | Grade 4                                                         |
|----------------------------------------------------------|-------------------------------------------------------------------------------------------------------|------------------------------------------------------------------------|----------------------------------------------------------------------------------------------------------------------------------------------------------------------|-----------------------------------------------------------------|
| Pain                                              | Do not affect or slightly affect physical activity                                                    | affect physical activity                                               | Affect daily life                                                                                                                                                    | Loss of basic self-care ability or hospitalization              |
| Induration
*, swelling
(optional)**
# | Diameter 2.5~<5 cm or area 6.25~<25 cm  and does not affect or slightly affect daily life | Diameter 5~<10 cm or area 25~<100 cm  or affect daily life | Diameter ≥ 10 cm or area ≥ 100 cm  or ulceration or secondary infection or phlebitis or aseptic abscess or wound drainage or seriously affect daily life | Abscess, exfoliative dermatitis, dermal or deep tissue necrosis |

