# the evaluation and grading of induration and swelling, rash and redness should be based on the functional level and the actual measurement results, and the indicators with higher classification should be selected.

Figure 4 Grading for systemic adverse events.

| Sign                                                         | Grade 1                                                                                       | Grade 2                                                                                      | Grade 3                                                                                                                              | Grade 4                                                                 |
|--------------------------------------------------------------|-----------------------------------------------------------------------------------------------|----------------------------------------------------------------------------------------------|--------------------------------------------------------------------------------------------------------------------------------------|-------------------------------------------------------------------------|
| Fever [Axillary temperature(°C)]
>14 years old | 37.3~<38.0                                                                                    | 38.0~<38.5                                                                                   | 38.5~<39.5                                                                                                                           | ≥39.5, last more than 3 days                                            |
| Gastrointestinal system                               |                                                                                               |                                                                                              |                                                                                                                                      |                                                                         |

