# Refers to Non-injection-site pain other than muscle pain, Arthralgia and headache

### General principles for the grading for other adverse events

The intensity of adverse events not mentioned in the rating table shall be evaluated according to the following criteria:

| Grade 1                                                                    | Grade 2                                                    | Grade 3                                             | Grade 4                                                | Grade 5 |
|----------------------------------------------------------------------------|------------------------------------------------------------|-----------------------------------------------------|--------------------------------------------------------|---------|
| Mild: Short-term
(< 48 hours) or
mild discomfort,
no influence on | Moderate: Mild
or moderate
restricted
activities, | Severe:
Significant
restricted
activities, | Critical:
Life-threatening
possibly,
severely | Death   |

| Grade 1                                   | Grade 2                                                                                                | Grade 3                                                                                 | Grade 4                                                  | Grade 5 |
|-------------------------------------------|--------------------------------------------------------------------------------------------------------|-----------------------------------------------------------------------------------------|----------------------------------------------------------|---------|
| activities,
treatment not
indicated | presentation
indicated
possibly,
treatment not
indicated or
mild treatment
indicated | presentation and
treatment
indicated,
hospitalization
indicated
possibly | restricted
activities,
intensive care
indicated |         |

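### Termination at 15% related grade 3 events is optional in the synopsis but mandatory in section 3.6, and fever of 39.5 °C or above lasting 3 days or less has no grade (minor wording corrections)

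*Combined protocol and SAP*

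**What the plan says.** **Termination.** In the synopsis, under the criteria for pausing or early termination, the termination list opens with "Investigators could terminate the study when any criteria for early termination is meet". It includes "Occurrence of grade 3 adverse events associated with vaccination in 15% of participants or more". Protocol 3.6 opens its own termination list with "The study will be terminated in advance if one of the following situations occurs", and item 2 there is the same criterion: "Occurrence of grade 3 adverse events associated with vaccination in 15% of participants or more (including injection-site reaction", followed by the same categories of reaction. Item 1 of that list (possibly related grade 4 reactions or SAEs) carries a clause leaving the decision to an expert group. Item 2 carries no such clause. Neither place says which participants form the denominator.

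**Enrolment.** The study plan in the synopsis, repeated in SAP 3.1, says that safety data are reviewed in real time and that further enrolment is suspended or terminated at once if a suspension or termination criterion is found.

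**Fever.** Protocol 5.5.2 states that events are "graded according to the guiding principles for the classification of adverse events in clinical trials of preventive vaccines", citing a national document, and then prints the tables. For axillary temperature, grade 1 is 37.3 to below 38.0 °C, grade 2 is 38.0 to below 38.5 °C and grade 3 is 38.5 to below 39.5 °C, all without a duration condition. Grade 4 is "≥39.5, last more than 3 days". The general scale at the end of 5.5.2 is restricted: "The intensity of adverse events not mentioned in the rating table shall be evaluated according to the following criteria".

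**Recording.** Under 5.5.1, participants are "asked to record the safety observation by themselves on the diary card till 14 days after the vaccination". Section 7.1 has researchers follow up, investigate retrospectively and review the diary cards.

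**The concern.** A stopping rule should give one answer when its threshold is reached. Here the investigators may terminate on one page and must terminate on another, for the same criterion, and the text supplied contains no rule of precedence between synopsis and body. The difference cannot be put down to loose drafting in 3.6: where that section wants discretion, as in item 1, it says so.

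The fever row matters because the grade feeds other rules. The 15% criterion explicitly covers systemic reactions and vital signs, and section 10.2.3.1 names fever among the common reactions. A scale on which a higher temperature can lose its grade is not monotone. Such an event has no category in the severity analysis of SAP 6.6. It may also drop out of the grade 3 counts, and it does not clearly fall under the care rule in 10.2.3.2 for reactions of grade 3 or above.

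**Working it through.** The plan gives no figure to reproduce. The check is a comparison of texts plus simple counts.

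**1. The 15% criterion**

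| | Synopsis | Protocol 3.6 |
|---|---|---|
| Force of the list heading | permissive (*could*) | mandatory (*will*) |
| 15% related grade 3 item | present, no qualifier | item 2, no qualifier |
| Grade 4 / SAE item | present, for probable association | item 1, for possible relation; expert group decides |
| New enrolment once a criterion is met | suspended or terminated (study plan; repeated in SAP 3.1) | not addressed |

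The trial gives a single dose, at V1. Suspending enrolment therefore stops new exposure whichever verb applies. What remains in conflict is whether the trial must then be formally terminated.

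**2. What the tiers are in participants**

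The denominator is not stated, so I show a range using the planned group sizes. The threshold is the smallest whole number at or above 0.10 × n or 0.15 × n.

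| Assumed n | 10% tier | 15% tier | One fewer, 10% tier | One fewer, 15% tier |
|---|---|---|---|---|
| 300 (all) | 30 | 45 | 29/300 = 9.7% | 44/300 = 14.7% |
| 200 (A + B) | 20 | 30 | 19/200 = 9.5% | 29/200 = 14.5% |
| 100 (A or B alone) | 10 | 15 | 9/100 = 9.0% | 14/100 = 14.0% |
| 50 (C or D alone) | 5 | 8 (0.15 × 50 = 7.5, rounded up) | 4/50 = 8.0% | 7/50 = 14.0% |

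The last two columns show that one uncounted participant matters only when the count sits exactly at a tier. That is true by construction. No event rate is assumed, so nothing here shows that a tier would be reached.

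**3. The fever row as printed**

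| Peak, duration | Grade |
|---|---|
| 39.4 °C, 1 day | 3 |
| 39.5 °C, 1 day | none |
| 39.5 °C, 3 days | none |
| 40.0 °C, 2 days | none |
| 39.5 °C, 4 days | 4 |

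This reads the grade 4 cell as requiring both the temperature and the duration, which is its natural sense. The general scale does not fill the gap, because it covers only events absent from the rating table and fever is in it.

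**4. When the gap has an effect**

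Any recorded reading of 38.5 to below 39.5 °C in the same episode gives grade 3. If the event is an SAE that may be related to vaccination, it meets the separate SAE criterion whatever its grade. The gap therefore affects the tier counts only when no reading in the grade 3 band is recorded, and it goes wholly untriggered only if the event is also not such an SAE. The protocol text does not exclude this, because it states no number of temperature readings per day. The diary card itself is a separate document and was not available.

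**The case against.** The strongest case against is that neither point has much practical reach.

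- **Exposure.** A reader might infer from the permissive synopsis heading that vaccination could continue past the 15% tier. The documents do not support that. The study plan and SAP 3.1 require enrolment to be suspended or terminated, each participant gets one trial dose, and under 3.6 the 10% tier already calls for an expert panel. The principal investigator, ethics committee and authority can each end the trial as well. All of this stands, and it confines the conflict to formal termination.
- **Oversight of high fever.** A reader might also infer that a fever of 40 °C would escape notice. That goes too far. Such a fever will usually pass through the grade 3 band, section 7.1 has researchers review the diary cards, 5.5.7 requires timely investigation, and 5.5.5 provides treatment where the investigator judges it necessary. A short fever is also not a missed grade 4 event, because the row as printed requires more than 3 days for grade 4.
- **Source of the gap.** The table presents itself as the scale of a national guideline. Whether the gap lies in that guideline or arose in transcription or translation cannot be settled from the documents, so it should not be called the authors' own choice. The trial still needs an explicit grade.
- **Reading the comma as *or*.** That would close the gap, but nothing in the text supports it. It would also make a single brief related fever of 39.5 °C a grade 4 reaction that meets the pausing criterion.

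What survives is that one criterion carries two different instructions and that one band of fever has no grade.

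**Conclusion.** Both points hold, at minor severity. For related grade 3 events in 15% or more of participants, the synopsis permits formal termination and section 3.6 requires it; stopping new exposure is not in dispute. Fever of 39.5 °C or above for 3 days or less has no grade. It therefore has no class in the SAP 6.6 severity analysis and is not counted toward the grade 3 tiers unless a reading of 38.5 to below 39.5 °C is also recorded. A possibly related SAE is still caught by its own criterion. At most the gap moves a count by the number of such participants, against tiers of 30 and 45 if n is 300 and 5 and 8 if n is 50. The conclusion rests on reading the grade 4 fever cell as a joint condition and on the diary card not fixing how often temperature is recorded. Endpoints, sample size and the immunogenicity analysis are unaffected.

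**What to change.** 1. **15% criterion.** State one action in both the synopsis and 3.6, for example that the study will be terminated, and name the denominator in the same sentence, for example participants vaccinated so far. Attach the wording to that item only. Changing the shared synopsis heading to a mandatory verb would also make the synopsis grade 4 and SAE item mandatory, contrary to the expert-group decision in 3.6.
2. **Grade 4 reaction and SAE item.** Treat possibly or probably related events the same way in both places: enrolment is suspended and the expert panel decides on termination. The study plan wording in the synopsis and SAP 3.1 can stay as it is.
3. **Fever row.** After checking the guideline cited in 5.5.2, grade fever of 39.5 °C or above lasting 3 days or less as grade 3.

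The cost is a small wording amendment. Because it touches participant safety, it needs ethics committee approval under section 7.2. No new procedures are needed.
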